## Abstract

**Background:**

The mental health impacts of workers within correctional settings has been of increasing focus over the past number of years. This paper outlines the study protocol for a trial that tests the efficacy of a brief resilience program, relative to a no intervention control in reducing general psychological distress and absenteeism in a cohort of correctional personnel in NSW, Australia.

**Methods:**

A, parallel, randomized controlled trial will be carried out in a small group format. Following informed consent, corrective personnel within prisons across NSW will volunteer to either attend a clinician delivered resilience program on stress management skills or not (*N* = 600). The primary outcome will be change in psychological distress including anxiety and depression at 2-months post intervention. Secondary outcomes include help-seeking behaviours and absenteeism.

**Discussion:**

This prevention focused treatment trial will assess whether a brief clinician delivered resilience program will reduce absenteeism and mitigate psychological distress in a cohort of corrective personnel within NSW, Australia. This study will yield insights into the role of a brief psychological program in mitigating the psychological distress reported by personnel in correctional settings.

**Trial registration:**

This trial was prospectively registered on the Australian New Zealand Clinical Trials Registry (ACTRN12622000029796).

**Ethics and dissemination:**

Ethics approval has been obtained from University of New South Wales Human Research Ethics Committee. Results of the trial will be submitted for publication in peer reviewed journals and findings presented at scientific conferences and to key service providers and policy makers.

## Background

Repeated exposure to threatening environments involving critical incidents and potentially traumatic events take a toll on one’s mental health. Research on the wellbeing of public safety personnel such as police, emergency service and correctional workers has been an increasing focus in recent years [1]. The nature of attending to critical events including death, threatened and actual violence, verbal altercations, self-injury, and inmate overcrowding on a routine basis can adversely impact mental health. One Canadian study revealed that up to one quarter of police, emergency service and corrections personnel screened positive for symptoms for post-trauma stress disorder and major depression [2]. These estimates parallel other international estimates of displaying that up one third of these personnel display mental health problems that meet diagnostic criteria [3, 4]. In particular, an increased frequency and duration of exposure to threatening environments can worsen health and mental health outcomes [5]. To this end, higher perceptions of threat and unpredictability reported by corrections personnel (than personnel in counterpart public safety occupations) may also contribute to this relationship between exposure to potentially traumatic events and negative mental health incidents [6]. Apart from heightened rates of mental disorders in corrective personnel [2], this cohort also reports suffering from physical ill health (i.e., stress related illness, ulcers, increased blood pressure), heightened work-home conflict (e.g., difficulties in separating work from home, fatigue, reduced time for family), job dissatisfaction and burnout [7, 8]. In turn, considerable monetary costs are associated with compensation claims owing to serious mental health conditions and related lost productivity and short and long-term absenteeism [9, 10].

Furthermore, challenges with the correctional organisation that are often cited provide a keen insight into the psychosocial environments surrounding corrective personnel. To this end, qualitative studies have highlighted that the nature of insecure employment (i.e., casual work), shift work, dissatisfaction with wages and interpersonal challenges with management [3, 11] can together add to sources of stress in corrective personnel. Here, reduced access to quality mental health care within the organizational structure, stigma, and perceptions of breach of confidentiality can together act as strong barriers to help-seeking [12]. To this end, the development of mental health interventions for this cohort must address help-seeking barriers and endeavour to work alongside the organizational and structural challenges such that meaningful change in mental health outcomes can be sought. Supporting this proposition is qualitative research suggesting that organizational acknowledgment of mental health challenges resulting from adversity within the workplace, coupled with the provision of mental health awareness and first aid training and programs for workers, are in keen demand as reported by workers [3]. As such, mental health programs that are supported by organizational structures may elicit engagement and motivation from corrective personnel, and in turn, provide a path to addressing important mental health challenges of this population.

The current study will assess the efficacy of a novel resilience training program that builds on a program developed by the World Health Organization (WHO) [13] to teach awareness about identifying stress, stress reduction strategies, problem management, and seeking/maintaining social support and connection. The program will be conducted in collaboration with Corrective Services New South Wales (CSNSW) and will be implemented within prison settings, wherein participation will be voluntary. This program will be compared against a no intervention control group that comprises repeated assessments to assess the efficacy of the resilience group overtime. This form of control condition was adopted because there is typically no resilience or stress reduction programs available in CSNSW for custodial staff, and so the rationale for this comparator was to test the efficacy of the intervention relative to current practices. In summary, this project takes a prevention perspective to test the efficacy of a potentially scalable program to reduce mental health problems in high-risk occupations, such as correctional facilities.

## Methods

### Aims & hypotheses

This study will assess the efficacy of a novel resilience training program supported with use of an app to practise learned stress reduction strategies. This Resilience Program is an adapted version of WHO’s Problem Management Plus (PM +) program [13], and designed from a prevention perspective to provide mental health awareness, and brief strategies for stress reduction in a cohort of corrective personnel across Australia. The randomized controlled trial (RCT) will compare this brief training program against a no intervention control group that will only undertake assessments at critical timepoints. Those receiving this resilience program are hypothesised to report lower levels of psychological distress, reduced absenteeism and increased help seeking relative to the a no intervention arm. The primary outcome measure is the Kessler Psychological Distress Scale-10 item version [14].

### Design & setting

This study is designed as a parallel RCT that will be conducted in prisons across NSW in Australia. The study will deploy a 2 (Treatment condition) × 3 (Assessment Point) factorial design. Participants will be assessed at baseline (T0),, at two-month follow-up (T1), and at six-month follow-up (T2), where T1 will be the primary outcome timepoint (see Fig. 1). This trial was registered on Australian New Zealand Clinical Trials Registry (ACTRN12622000029796) on 14 January 2022 and received ethical approval from the University of New South Wales Human Ethics Panel C, Australia. The Resilience Program will provide 2 × 2-h sessions administered by clinical psychologists one month apart, delivered in groups of 10–15 people.

**Fig. 1 Fig1:**
[figure not shown]
Flow diagram of study

### Participants, recruitment and informed consent

Six hundred Corrective Services personnel will be identified through prisons across NSW. Participants will be of minimum 18 years of age and currently be employed by Correctional Services NSW. As this is a preventative intervention, the presence of psychological distress will not be a requirement of entry into this trial. Informed consent will be obtained both verbally and in written form, where the former will be essential prior to personnel taking part in the resilience training session. At the time of written consent, participants will complete the pre-assessment (T0) consisting of the K10 and help-seeking behaviour. Recruitment commenced in March 2022.

### Randomization

Prison personnel within eight prison settings across NSW will be allocated to either the resilience program or no control intervention on a 1:1 basis (no block randomization). This will be carried out on a computerized software by a research assistant who is independent to any other aspects of the intervention. This randomization will take place prior to the completion of the T0 assessment. No blinding will be used for the participants and clinical psychologists delivering the interventions.

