### Analysis

Personnel analysing the data from this trial will be blinded to group allocation. A total of 600 Corrective Services Personnel will be included in the trial. Power calculations were conducted using GPower 3.1.9.7 to determine the between treatment condition effect at follow-up on the premise of a small effect size. This calculation indicated a minimum sample size of 270 participants per group (power = 0.95, alpha = 0.05, two-sided). On the basis of 10% attrition at follow-up, it was estimated that 600 participants (300 per group) were needed.

Analyses will focus primarily on intent-to-treat analysis. Using SPSS version 28, hierarchical linear mixed models will be used to study differential effects of each treatment condition because this method effectively handles missing data by calculating estimates of trajectories. Fixed (intervention, time of assessment) effects and their interactions will be considered in the unstructured models, which will provide an index of the relative effects of the treatments; time of assessment will include baseline, posttreatment, and 3-month follow-up. For the follow-up analyses between the two conditions, analyses will focus on linear time effects, treatment conditions, and interactions. Fixed effects parameters were tested with the Wald test (t-test, *p* < 0.05, two-sided) and 95% confidence intervals. Cohen’s (d) effect size was calculated for all analyses. The primary outcome measure will be the K10. The primary outcome timepoint will be the 6 months assessment. As baseline assessments are incorporated into this modelling, the likelihood of no data is zero. To this end, missingness will be tested at random by assessing baseline characteristics of those do and do not drop out from the study.

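### Randomisation is placed before the baseline K10 and the written consent that accompanies it, in unblinded staff, so entry and T0 answers may depend on the allocated arm

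*Protocol article*

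**What the plan says.** Four parts of the protocol article bear on the order of events.

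- **Randomization:** "This randomization will take place prior to the completion of the T0 assessment". The same section adds "No blinding will be used for the participants and clinical psychologists delivering the interventions". An independent research assistant generates the allocation by computer.
- **Participants, recruitment and informed consent:** "At the time of written consent, participants will complete the pre-assessment (T0) consisting of the K10 and help-seeking behaviour". Consent is both verbal and written. Of the two, it is the verbal form that is tied to a later step: "where the former will be essential prior to personnel taking part in the resilience training session".
- **Abstract, Methods:** "Following informed consent, corrective personnel within prisons across NSW will volunteer to either attend a clinician delivered resilience program" or not. This puts some form of consent first, but does not say whether it is the written form, or where allocation falls.
- **Analysis:** the primary approach is intent-to-treat. A mixed model has intervention, time and their interaction as fixed effects, and baseline is one of the time levels. Because baseline is in the model, the section concludes that "the likelihood of no data is zero".

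**The concern.** A baseline is safe to use as a pre-treatment value when it is recorded before anyone can know the allocation. Here the stated order is the reverse, the participants are unblinded, and the instrument is a self-report scale that is also the primary outcome. Two things could then differ by arm for reasons other than chance.

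1. **T0 answers.** Relief, expectation or disappointment about the assigned arm may colour how a person rates the past four weeks.
2. **Entry.** The comparator is no intervention. Someone who learns of that assignment may decline written consent or skip T0 more readily than someone offered the program.

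The first distorts the baseline leg of the treatment contrast. The second changes who is compared. The planned missing-data check cannot see the second, because it compares the baseline characteristics of people who do and do not drop out, and a person who never completed T0 has no baseline K10 to compare. Neither the independent generation of the sequence nor the blinding of analysts protects against these two routes.

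**Working it through.** **Step 1. Order of events.** Allocation precedes completion of T0 (Randomization). T0 coincides with written consent (Participants). Together, allocation may precede written consent as well as T0. No section states that allocation is concealed until then.

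**Step 2. The plan's own sample size, to set a scale.** Inputs from the Analysis section: 270 per group, power 0.95, two-sided alpha 0.05, 10% attrition.

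- 270 / (1 − 0.10) = 300 per group, 600 in total, which reproduces the stated target.
- The small effect is given no number. The implied standardised difference is d = (1.960 + 1.645) × √(2/270) = 3.605 × 0.0861 ≈ 0.31.

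**Step 3. How a T0 shift enters the effect.** With baseline as a level of time, the interaction contrast at a follow-up visit is

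(follow-up mean − T0 mean, program) − (follow-up mean − T0 mean, control).

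If knowing the arm changes the between-arm T0 difference by b and leaves follow-up answers unchanged, the contrast moves by b in the opposite direction. The documents give no value for b. Assumed range:

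| Assumed b (SD) | Share of d ≈ 0.31 | If it works against a true 0.31 |
|---|---|---|
| 0.05 | 0.05/0.31 ≈ 0.16 (about one sixth) | 0.31 − 0.05 = 0.26 |
| 0.10 | 0.10/0.31 ≈ 0.32 (about one third) | 0.31 − 0.10 = 0.21 |

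**Step 4. What this does to the test when there is no true effect.** Assume 270 per arm, a T0-to-follow-up correlation ρ of 0.5 to 0.7, and a simple change contrast with SE = √(2(1 − ρ)) × √(2/270). The two-sided rejection rate is Φ(b/SE − 1.960) + Φ(−b/SE − 1.960).

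| b (SD) | ρ = 0.5 | ρ = 0.6 | ρ = 0.7 |
|---|---|---|---|
| 0.05 | 8.9% | 10.0% | 11.7% |
| 0.10 | 21.3% | 25.5% | 32.3% |

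The nominal rate is 5%. These rates count rejections in both directions.

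**Step 5. Direction.** If expectation lowers reported distress at T0 in the program arm, or disappointment raises it in controls, the contrast is biased against the program. A shift the other way favours it. The documents do not settle which is more likely.

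**Step 6. Arm-dependent entry.** If a fraction q of one arm is lost and differs from the rest by m SD, that arm's mean moves by q × m. With assumed values q = 0.10 and m = 0.5, this is 0.05 SD; with q = 0.20 and m = 0.5, it is 0.10 SD. If the difference is stable over time it also appears at T0 and largely cancels in a change contrast.

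**Step 7. Who is lost from the model.** T0 is an outcome row, not a covariate. A randomised person with a follow-up K10 but no T0 still contributes. A randomised person with no assessment at all, such as someone who refuses written consent, contributes nothing. The zero-likelihood statement therefore fails for that group, and only for that group.

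**The case against.** The Randomization section dates the act of randomising, not the moment when staff are told the result. The sentence on blinding describes the trial as a whole. Allocation could be generated early and released only after T0. The abstract places informed consent first, and verbal consent may precede allocation, so staff may have committed to the trial before any arm existed. The flow diagram and the full protocol are not shown, and either could settle the order.

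Most of this stands, and it limits the point to a risk. It does not remove it, because the order is stated affirmatively, written consent is tied to T0, and nothing shown says the result is held back.

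A reader might also infer more than the documents support:

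- **That staff knew their arm before T0.** Disclosure is never dated.
- **That staff choose their arm**, since the abstract says they "will volunteer to either attend a clinician delivered resilience program on stress management skills or not". The same abstract, the aims and the design section all describe a randomised trial, so this reads as loose drafting.
- **That everyone without a T0 leaves the analysis.** The mixed model keeps anyone with a follow-up value.
- **That a 0.10 SD shift is half the target effect.** That presumes d = 0.2, which the article never states; its sample size implies about 0.31.
- **That adjusting for T0 as a covariate would shrink the bias.** No such analysis is planned.

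**Conclusion.** The point holds as a weakness in the stated order. It permits arm-dependent entry and arm-dependent baseline reporting, and the article describes no safeguard against either. Whether either occurred cannot be told from the text, so it would be too strong to say that randomisation has lost its protection.

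The one-for-one transfer follows from the planned model as long as a T0 shift does not persist to follow-up. Its size rests entirely on assumption: 0.05 to 0.10 SD would be about one sixth to one third of the implied d of about 0.31, and could hide a benefit as easily as create one. Separately, and whatever the size of any bias, the claim that no participant can be without data is not guaranteed for people randomised before they have supplied anything.

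**What to change.** **Staff not yet randomised.** Amend the Randomization section along these lines: randomisation takes place after written consent and completion of the T0 survey. If groups must be planned ahead, at least state that the research assistant releases no allocation until both are done. T0 is the K10 and one help-seeking question, so this is feasible.

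**Staff already randomised** (recruitment began in March 2022). State when allocation was disclosed. Report by arm the numbers randomised, giving written consent and completing T0, with everyone randomised in the denominator. Add a sensitivity analysis that compares follow-up K10 between arms without using T0. This addresses shifted T0 answers but not arm-dependent refusal, for which the counts by arm are the only evidence.

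**Analysis section.** Replace the zero-likelihood statement with one acknowledging that a randomised person with no assessment contributes no data, and say how such people will be reported.

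**Cost.** A procedural amendment with ethics approval and slightly later scheduling of groups. Changing the order mid-trial creates two cohorts with different baseline timing, which should be identified in the report. The analysis without T0 may be less precise: under the assumptions above its SE is √(2/270) = 0.086 SD, against 0.086 SD for the change contrast at ρ = 0.5 and √0.6 × 0.086 = 0.067 SD at ρ = 0.7.

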### Intervention

#### Resilience program

The Resilience program will be administered in a face-to-face group format consisting of 10–15 people over two 2-h group sessions (one month apart). These sessions will consist of an educational and group discussion format with content consisting of stress coping strategies delivered by clinical psychologists: anxiety reduction, problem solving, behavioral activation, and accessing social support. Following the sessions, participants will be instructed to download an app, named *Headgear* [15] that was developed by the BlackDog Institute to support resilience building and better wellbeing. This app will provide additional skills in anxiety reduction, mindfulness, and behavioural activation. This app will function as an ongoing self-help aid to be used at the participants’ discretion. Specifically, instructional prompts in this app will guide participants’ use of strategies and this will be available in an ongoing basis for the duration of the study. Adherence will be assessed by monitoring participants' attendance at each session via a checklist maintained by the clinical psychologist.

#### No intervention

The control condition will engage in repeated assessments across T0, T1, and T2.

### Primary outcome

The Kessler-10 (K-10) is a well validated indicator of psychological distress [14] and comprises of 10 questions about general wellbeing, experience of emotional states including symptoms of depression and anxiety over the past four weeks. Items are scored on a 5-point scale (range 0 to 50; higher scores indicate higher levels psychological distress), where a cut off of 20 [16] will be used to indicate the presence of psychological distress.

### Secondary outcomes

Participants will self-report their help-seeking behaviours using a single dichotomous questions asking if participants have sought assistance for mental health issues in the past six months. The trial will also assess absenteeism as measured by sickness leave from Department of Corrective Service work records, where this will be collected at T2*.*

### Data oversight & management

Study implementation procedures will be monitored on an ongoing basis by the trial management committee consisting of the principal investigator, co-investigators, and local research coordinators. All adverse events that take place during the trial will be monitored by the facilitators at each session, whereby any reported adverse events will be referred to the UNSW Human Ethics Committee and Trial Sponsor. Further, assessments using the K10 were used to detect severe distress and relevant participants were contacted and recommended referral resources.

All participants will be required to have their identities known to the study as they will be followed up for trial assessments at two- and six-month follow-up assessments (T1 & T2). All data from pre-treatment, and follow-up online surveys will be entered on an electronic database in a deidentified manner in which participants are allocated a unique identification number. Restricted access will be made available to research staff directly involved in the study. AES-256 bit encryption will be used move any data from one electronic location to another. The research staff working on the project will initially have access to the data via the UNSW Research Long Term Data Store Interface. Any study protocol amendments will be approved by the local ethics committee prior to implementation. All investigators and participants enrolled in the trial will be informed.

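### Apart from the K10 severe-distress check, adverse events are captured only at resilience sessions, so other harms are not ascertained in controls, or in either arm after session 2

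*Protocol article*

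**What the plan says.** Data oversight & management sets the scope, the observer and the occasion of adverse-event capture in one sentence: "All adverse events that take place during the trial will be monitored by the facilitators at each session". It then says that "any reported adverse events will be referred to the UNSW Human Ethics Committee and Trial Sponsor". The next sentence adds a separate check: "assessments using the K10 were used to detect severe distress and relevant participants were contacted and recommended referral resources".

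Who attends sessions is fixed elsewhere. Under Design & setting, "The Resilience Program will provide 2 × 2-h sessions administered by clinical psychologists one month apart". The Intervention section adds that a self-help app stays open to the resilience arm throughout the study. Under No intervention, "The control condition will engage in repeated assessments across T0, T1, and T2"; no session or facilitator contact is described for that arm. Assessments fall at baseline (T0), two months (T1) and six months (T2).

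**The concern.** The sentence on adverse events claims complete coverage of the trial, but the occasion it names arises in one arm only and ends early. A control participant never meets a facilitator. A resilience participant meets one at most twice, and then continues with the app for several months without further contact of that kind.

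Two things are at stake. The ethics committee and the sponsor receive what this route produces, and could take it for a picture of the whole trial. And if the trial report gives adverse events by arm, the counts will differ partly because one arm was asked and the other was not. A late unwanted effect of the program could go unrecorded, and its absence could be read as evidence of safety. The Discussion raises the prospect of wider roll-out, so a sound statement on harms has practical value.

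**Working it through.** The article gives no figure on this point to reproduce. The check sets the capture rule beside each arm's schedule of contacts.

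**Inputs**
- Capture rule: facilitators, at each session (Data oversight & management).
- Sessions: two, one month apart, resilience arm only (Design & setting; Resilience program).
- Control contacts: T0, T1 and T2 assessments only (No intervention).
- Follow-up: to six months (Design & setting).
- K10 check for severe distress: no restriction by arm (Data oversight & management); the K10 asks about the past four weeks (Primary outcome).

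**Facilitator contacts per participant**
- Resilience arm: 2, if both sessions are attended.
- Control arm: 0.

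**Share of follow-up after the last facilitator contact, resilience arm**

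The article does not say when session 1 falls relative to T0, so this rests on an assumption. The share is (length of follow-up − time of session 2) / length of follow-up.
- Session 1 near T0, six months counted from T0: session 2 is at month 1, and (6 − 1)/6 = 0.83.
- Six months counted from session 2, so seven months from session 1: (7 − 1)/7 = 0.86. The Abstract, which places the primary outcome two months after the intervention, fits this reading.
- Session 2 as late as T1, six months counted from T0: (6 − 2)/6 = 0.67. This is a lower bound if T1 follows the sessions.

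Under each of these timings, most of the follow-up lies after the facilitator route has closed.

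**What the K10 check adds**
- It reaches both arms at all three assessments. T1 and T2 fall after session 2 under the first two timings, and T2 does under all three.
- It concerns distress only. Other unwanted effects have no place in it.
- Each K10 looks back four weeks. Taking four weeks as about one month, the T1 and T2 windows cover about 2 of the 6 months.
- The article gives no threshold for severe. The cut-off of 20 under Primary outcome marks the presence of distress.
- The stated consequence is contact and referral advice. The article does not say that these cases are recorded or reported as adverse events.

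**Side by side**

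| Harm | Resilience, to session 2 | Resilience, after session 2 | Control, throughout |
|---|---|---|---|
| Severe distress | Facilitator and K10 | K10 | K10 |
| Any other harm | Facilitator | No stated route | No stated route |

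The imbalance lies in the second row.

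**The case against.** The strongest answer is that the article does not rely on facilitators alone. The K10 check covers both arms to six months, and distress is arguably the most relevant harm of a stress-management program. The primary K10 analysis would itself show worsening in either arm, and sick leave from work records is planned at T2. All of this stands, and it limits the point to harms other than severe distress.

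A reader might infer that controls have no safety monitoring at all, or that harms cannot be compared between arms. The documents do not support either: severe distress is checked in both arms and can be tabulated from data already planned.

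A reader might also infer that a planned safety comparison is biased, or that the record will show a marked excess of events under the program. The article plans no between-arm test of harms and gives no event rate. The same short capture window would also hold down the resilience arm's count, so the size of any imbalance cannot be stated. Nor does the article say that events volunteered outside sessions would be turned away.

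Finally, a journal article is condensed, and the full protocol may describe adverse-event forms and reporting by controls. That would excuse missing detail. It excuses less here, because the article itself fixes scope, observer and occasion, and these do not fit its own contact schedule. Even if a fuller procedure exists, the published sentence needs correcting.

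**Conclusion.** The point holds in a limited form. As written, the stated route cannot capture every adverse event in the trial. Apart from the K10 severe-distress check, it reaches no control participant and nobody after session 2. In the resilience arm the uncovered period is about 5 of 6 months (83%) if session 1 is near T0, with a range of 67% to 86% over the other timings considered. Any by-arm count of adverse events drawn from this route would be asymmetric by design.

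The conclusion assumes that the article describes all the routes in use. It does not touch the primary analysis of the K10. This is a worthwhile, low-cost improvement to safety ascertainment and reporting, and not a flaw that endangers the trial's main result.

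**What to change.** 1. Add the same short adverse-event or unwanted-effect item to the T1 and T2 surveys in both arms. The vehicle exists: "All data from pre-treatment, and follow-up online surveys will be entered on an electronic database". Base any by-arm summary of harms on this item.
2. Tabulate by arm the number of participants whose K10 worsened to the severe level. State the threshold that the trial already uses for contacting participants, since the article does not give it. This needs no new data.
3. Keep facilitator reports as a supplementary source in the resilience arm, and state that they are not used to compare arms.
4. Reword the sentence in Data oversight & management so that its scope matches the routes in use.

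The cost is one or two survey items at each of T1 and T2, one descriptive table, more reports to process and a minor ethics amendment. Recruitment began in March 2022, so some participants may pass T1 or T2 before the item is in place. In that case, report how many in each arm were asked. The K10 table and a plain statement of the limitation remain possible for everyone with K10 data.
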